### 3.5 Per-Protocol (PP) Population

The Per-Protocol (PP) Population will include all patients of the IIT population, excluding patients with important protocol deviations that may affect the statistical analysis. The following patients will be excluded by default:

- Patients who receive an IMP different to the IMP assigned by randomization
- Patients who receive less than 80% of the planned dose
- Patients who significantly violate inclusion/exclusion criteria

### 3.6 Subgroup analyses

Due to the exploratory character of this pilot study efficacy and selected safety results will further be investigated within selected subgroups. This will be done to detect possible relationships that procedural or patient characteristics may have on the response parameters.

If the levels of subgroups (e.g. surgery types) are too numerous to form subgroups of sufficient size, the influence of the characteristic will be studied using model-based exploratory analyses (e.g. logistic regression [especially assessing the influence of IMP compliance on treatment response], Analysis of Covariance, Proportional hazards regression).

Presently, subgroup analyses are planned based on the following characteristics: sex; complexity of procedure (simple versus complex); and urgency of procedure (elective versus non-elective).

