**Sample Size and Statistical Analysis Plan:**

The study will include 120 randomized patients, which, accounting for randomized but untreated patients in both arms, is expected to provide at least 100 evaluable patients, with 50 in each arm. The sample size determination was based on pragmatic reasons, no statistical sample size estimation was performed.

In general, descriptive statistics with 95% exploratory confidence intervals will be used to describe the data. Simple tests of comparison will be used to compare outcomes between the two groups. To detect trends of

|                                                                      |                                               |
|----------------------------------------------------------------------|-----------------------------------------------|
| Name of Sponsor:
[name], Toronto General Hospital |                                               |
| Name of Investigational Product:
Octaplex           | Protocol Identification Code:
FARES |
| Name of Active Ingredient:
Prothrombin complex concentrate | Date of Final Protocol:                |

a different efficacy or safety pattern, the relationship of efficacy and safety endpoints with procedural or patient characteristics will be explored. For this, descriptive statistics within subgroups or model-based exploratory testing and confidence intervals will be computed.

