### 9.2.2 Subgroup Analysis

Due to the exploratory character of this pilot study efficacy and selected safety results will further be investigated within subgroups.

This will be done to detect possible relationships that procedural or patient characteristics may have on the response parameters.

If the levels of subgroups (e.g. surgery types) are too numerous to form subgroups of sufficient size, the influence of the characteristic will be studied using model-based exploratory analyses (e.g. logistic regression, Analysis of Covariance, Proportional hazards regression).

Details on the subgroup and model-based inferences will be given in a Statistical Analysis Plan that will be finalized before the Data Review Meeting.

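### For sex, complexity and urgency the plan gives results within each subgroup, but no estimate of how far the PCC–FP difference varies between subgroups

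*Combined protocol and SAP*

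**What the plan says.** - **Protocol synopsis, Sample Size and Statistical Analysis Plan.** The stated target is this: "a different efficacy or safety pattern, the relationship of efficacy and safety endpoints with procedural or patient characteristics will be explored". Two kinds of tool are then named, in these words: "descriptive statistics within subgroups or model-based exploratory testing and confidence intervals will be computed".
- **Protocol 9.2.2.** Here "efficacy and selected safety results will further be investigated within subgroups". The particulars are deferred: "Details on the subgroup and model-based inferences will be given in a Statistical Analysis Plan".
- **SAP 3.6.** Here "efficacy and selected safety results will further be investigated within selected subgroups". The purpose given is: "This will be done to detect possible relationships that procedural or patient characteristics may have on the response parameters". The planned factors are "sex; complexity of procedure (simple versus complex); and urgency of procedure (elective versus non-elective". If a factor has too many levels to split, "the influence of the characteristic will be studied using model-based exploratory analyses", with logistic regression, analysis of covariance and proportional hazards as example model families. No model terms are listed, apart from a remark on the influence of IMP compliance on treatment response.
- **SAP 4.6.** Endpoints are compared between the two arms by Fisher's exact test, t-test or negative-binomial regression. No subgroup factor enters these comparisons.

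In both documents the word interaction occurs only in the sense of drug interaction. No section names a heterogeneity test, or a confidence interval for a difference between subgroup effects.

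**The concern.** In a two-arm trial, the natural reading of a different efficacy pattern across patient types is that the PCC–FP difference changes with the type of patient. The quantity that answers this is the contrast between the subgroup-specific treatment effects. A result within one subgroup answers another question: whether PCC and FP differ there. Two such results side by side do not say how far the effects differ, or how uncertain that difference is.

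The three named factors have two levels each, so the model route in SAP 3.6 would not normally be triggered for them. For these factors the within-subgroup display is therefore the whole specified analysis. The risk is that an effect seen clearly in one stratum and not in the other is taken as a different pattern when the underlying effect is the same in both. The pilot's stated objective is to inform the design of Phase 3, so such a misreading would be unhelpful.

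**Working it through.** **No figure in the plan to reproduce.** Neither document states power or precision for a subgroup analysis. The 120 randomized and 100 evaluable patients are described as a pragmatic choice without statistical estimation.

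**Inputs.**
- From the documents: 50 evaluable patients per arm (protocol 9.1), two-level factors (SAP 3.6), Fisher's exact test for proportions (SAP 4.6), two-sided 95% intervals (SAP section 4).
- Assumed: response rates, and an even split, which gives 50 / 2 = 25 patients per arm in each subgroup (four cells of 25).

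**Step 1: discordant subgroup results when the effect is uniform.** Let *s* be the exact probability that Fisher's test gives p < 0.05 in one subgroup of 25 versus 25. The two subgroups are independent, so the chance that exactly one is significant is 2 × *s* × (1 − *s*).

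| Assumed FP vs PCC response, same in both subgroups | *s* | 2*s*(1 − *s*) | Interaction test signals |
|---|---|---|---|
| 55% vs 80% | 0.361 | 2 × 0.361 × 0.639 = 46% | 3.9% |
| 60% vs 80% | 0.231 | 2 × 0.231 × 0.769 = 36% | 3.9% |
| 60% vs 75% | 0.130 | 2 × 0.130 × 0.870 = 23% | 4.4% |
| 60% vs 70% | 0.070 | 2 × 0.070 × 0.930 = 13% | 4.7% |

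The interaction test is the Wald statistic (log OR₁ − log OR₂) / √(V₁ + V₂), with 0.5 added to each cell, at two-sided 0.05. With a 70/30 split at 60% versus 80%, simulation of 20,000 trials gives 39% discordance and a 3% interaction signal.

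**Step 2: does discordance carry information?** Take a true reversal: FP 50% and 70%, PCC 70% and 50% in the two subgroups. Discordance is again 36%, the same as for a uniform 60% versus 80%. The interaction test signals in 54%.

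**Step 3: what the interaction estimate can show.** On the risk-difference scale with four cells of 25, SE = √(4 × p(1 − p) / 25).
- Rates near 70%: SE = √(4 × 0.21 / 25) = 0.183. The 95% CI half-width is 1.96 × 0.183 = 36 points. The difference in effects detectable with 80% power is (1.96 + 0.84) × 0.183 = 51 points.
- Rates near 50%: SE = √(4 × 0.25 / 25) = 0.200, and the detectable difference is 2.80 × 0.200 = 56 points.
- If PCC works in one subgroup only (FP 60% in both, PCC 85% and 60%), interaction power is 28%.

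**The case against.** The strongest reply is that the plan promises less than the concern supposes, and much of it stands.

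- **The aim is open to another reading.** Protocol 9.2.2 and SAP 3.6 speak of relationships between characteristics and response, which a prognostic model answers. The mismatch is with the synopsis phrase about a different pattern.
- **Per-stratum tests are not promised.** The synopsis says descriptive statistics within subgroups, and SAP section 4 calls the methods primarily descriptive. The 13% to 46% applies only if the SAP 4.6 comparisons are repeated by subgroup and read side by side.
- **The model terms are open.** A reader might infer that the SAP commits to main-effect models that cannot see effect modification. It names model families only, and an interaction term is not excluded. This is an omission in the specification.
- **A reversal would not be invisible.** A reader might infer that it would. For the three planned factors both arms' results are shown in each stratum. With 55% to 80% in one stratum and 80% to 55% in the other, each observed difference has the right sign with probability 0.963, so the two have opposite signs in about 0.963² = 93% of trials.
- **Phase 3 eligibility.** A reader might infer that subgroup findings will set eligibility or stratification. No section says so. Protocol 1.2 lists feasibility, design, primary outcome, sample size and early safety issues.
- **Low power.** With 25 patients per cell, an interaction test misses all but very large differences. This is true. It argues for showing the interval, so that the imprecision is visible, and against treating a non-significant interaction as evidence of uniformity.

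What the reply does not supply is a planned estimate of the between-subgroup difference. Protocol 9.2.2 left that detail to the SAP, and SAP 3.6 does not give it.

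**Conclusion.** The point holds as a modest gap in specification. For sex, complexity and urgency, nothing planned estimates how far the PCC–FP difference varies, although the synopsis names a different pattern as the target. The size depends on use: with 25 per cell, side-by-side significance misleads in about 13% to 46% of trials over the assumed rates, against about 4% for an interaction test. The percentages rest on assumed response rates and, except for the one 70/30 check, an even split; only the sample size and the factors come from the documents. The analyses are exploratory and make no power claim, so the trial's main conclusions are not affected. The case for changing the text is that an interaction estimate with its interval is a better method than side-by-side results and uses data already collected.

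**What to change.** In SAP 3.6, with a matching sentence in protocol 9.2.2:

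1. For each of the three factors, fit one model per primary endpoint with treatment, characteristic and treatment-by-characteristic: logistic for P1 and P3, and the already planned negative-binomial model for P2.
2. Report the interaction estimate with its 95% CI beside the PCC–FP estimate and CI in each subgroup.
3. Base any statement of a different pattern on the interaction estimate, not on significance in one subgroup and its absence in the other.
4. State that precision is low (80% power only for a difference in effects of about 50 points), so that results are hypothesis-generating.

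Two limits should be written in. The change should not extend to factors with many levels, where cells would be too sparse at about 100 patients. For P3 it suits components such as RBC. SAP 6.1 counts FP as an allogeneic product, so almost no treated FP-arm patient can be free of all products, and an odds ratio for that total is not usefully estimable.

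The cost is a few lines of SAP text and one extra model term, with no new data. The drawback is wide intervals, about ±36 points at response rates near 70%. The proposal covers P1 to P3; it does not address the selected safety results, which would stay descriptive.

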## 4 STATISTICAL ANALYSES

All statistical analyses will be performed using the SAS® software (Version 9.4 or later).

The analysis of safety will be based on the SAF and additionally on the ITT population.

The primary evaluation of overall efficacy will be performed on the ITT population. In addition selected efficacy analyses will also be presented for the PP population.

If not stated otherwise the following standard descriptive statistics will be presented:

#### – Descriptive statistics for continuous data

N, mean, SD, min, lower quartile, median, upper quartile and max will be presented. These descriptive statistics will be determined for measured values and optionally for differences to baseline.

#### – Descriptive statistics for categorical data

Absolute frequencies and percentages will be presented. Percentage bases (denominators) will be identified in the table title or footnote (i.e. all subjects at risk, all non-missing cases, all cases). For changes from baseline, shift tables may be generated.

#### – Exploratory statistics

|                           |                 |             |               |
|---------------------------|-----------------|-------------|---------------|
| Statistical Analysis Plan | Version 2.0     |             | Page 11 of 19 |
| Sponsor                   | [name] | Protocol No | FARES         |

Although statistical methods are primarily descriptive, two-sided 95% confidence intervals may be presented for selected parameters (e.g. incidences of adverse events) in an exploratory manner.

– Listings

All recorded data will be listed by subject. Identification variable will be the subject ID.

Derived data will be stored in special analysis data sets and will be calculated as outlined in section 6.1.

## 4.1 Conventions

### 4.1.1 Baseline definition

Baseline will be defined as the last value on or prior to the first IMP administration.

### 4.1.2 Missing data

No imputations for missing data will be performed.

### 4.1.3 Pooling of centers

No pooling of centers will be performed (only two centers are involved in the study).

## 4.2 Demographic and other background data

### 4.2.1 Basic description

All available demographic data (sex, age, height, weight, and Body Mass Index (BMI)) will be summarized in appropriate tables (summary statistics or frequency tables) for the ITT and PP populations.

## 4.3 IMP exposure, compliance

Dose and frequency of IMP administrations of PCC or FP will be summarized in appropriate tables (summary statistics or frequency tables) for the ITT and PP populations.

## 4.4 Medical history

Medical history findings will be coded using the MedDRA thesaurus in the version current at the time of study start. Coding will be performed by the CRO and agreed upon with the sponsor before database lock. (cf. DMP). The summary tables will display the medical history findings for pre-specified conditions by MedDRA System Organ class (SOC) and Preferred term (PT). Displays will be presented for the ITT and PP populations. Other medical history texts will only be listed.

## 4.5 Prior and concomitant medication

Medications will be coded using the WHO Drug Global thesaurus in the version current at the time of study start. Coding will be performed by the CRO and agreed upon with the sponsor

|                           |                 |             |               |
|---------------------------|-----------------|-------------|---------------|
| Statistical Analysis Plan | Version 2.0     |             | Page 12 of 19 |
| Sponsor                   | [name] | Protocol No | FARES         |

before database lock. (cf. DMP). For concomitant medications tables will show the frequencies of subjects by WHO preferred term. Prior medication will only be listed.

#### 4.6 Efficacy

The primary population for the analysis of the efficacy of the IMPs will be the ITT. The primary efficacy endpoints will also be analyzed for the PP population.

The analysis of efficacy will focus on the following primary endpoints:

P1. Treatment response, defined as effective if no additional hemostatic intervention (such as administration of hemostatic agents including a second dose of IMP, platelet transfusion, or surgical re-exploration) in the time windows

- from 60 minutes to 4 and 24 hours after initiation of the first dose of IMP,
- *from initiation of the first dose of IMP to 4 and 24 hours.*

Otherwise, treatment response will be considered as not effective, see section 6.1. If the dose of IMP is repeated within less than 60 minutes, treatment response to the IMP will be assessed for the time frames after the second IMP dose only.

P2. Amount of allogeneic blood products (for each type of product and cumulatively) administered

- during the first 24 hours after the start of surgery,
- *during the first 24 hours after the end of CPB,*
- *during the first 24 hours after randomization,*
- *during the first 24 hours after the start of first IMP dose.*

P3. Number of patients who do not receive any allogeneic blood product (in total and for each type separately)

- during the first 24 hours after the start of surgery,
- *during the first 24 hours after the end of CPB,*
- *during the first 24 hours after randomization,*
- *during the first 24 hours after the start of first IMP dose.*

In addition the following efficacy endpoints will be explored:

S1. Number of partial or full IMP doses of PCC and FP administered

- during the first 24 hours after the start of surgery.
- *during the first 24 hours after the end of CPB,*
- *during the first 24 hours after randomization,*
- *during the first 24 hours after the start of first IMP dose.*

|                           |                 |             |               |
|---------------------------|-----------------|-------------|---------------|
| Statistical Analysis Plan | Version 2.0     |             | Page 13 of 19 |
| Sponsor                   | [name] | Protocol No | FARES         |

S2. Incidence of major bleeding, using the universal definition of perioperative bleeding (UDPB) in cardiac surgery scores and their individual components

- during the first 24 hours after start of surgery,
- *during the first 24 hours after the end of CPB,*
- *during the first 24 hours after randomization,*
- *during the first 24 hours after the start of first IMP dose.*

as well as a modified version of the UDPB not including PCC and FP requirements.

S3. Amount of allogeneic blood products (for each type of product and cumulatively)

- from start of surgery to postoperative day 7,
- *from end of CPB to postoperative day 7,*
- *from randomization to postoperative day 7,*
- *from start of first IMP dose to postoperative day 7.*

S4. Number of patients who do not receive any allogeneic blood product (in total and for each type separately)

- from start of surgery to postoperative day 7.
- *from end of CPB to postoperative day 7,*
- *from randomization to postoperative day 7,*
- *from start of first IMP dose to postoperative day 7.*

S5. Number of patients receiving recombinant activated factor VII (rFVIIa)

- during the first 24 hours after the start of surgery
- *during the first 24 hours after the end of CPB,*
- *during the first 24 hours after randomization,*
- *during the first 24 hours after the start of first IMP dose.*

S6. Number of patients receiving fibrinogen concentrate

- during the first 24 hours after the start of surgery.
- *during the first 24 hours after the end of CPB,*
- *during the first 24 hours after randomization,*
- *during the first 24 hours after the start of first IMP dose.*

S7. Change in coagulation parameters (INR, ROTEM [EXTEM CT and MCF] and fibrinogen levels) within 75 minutes before and after IMP administration, where performed as part of standard of care.

S8. Time elapsed from first IMP administration to time leaving the operating room.

|                           |                 |             |               |
|---------------------------|-----------------|-------------|---------------|
| Statistical Analysis Plan | Version 2.0     |             | Page 14 of 19 |
| Sponsor                   | [name] | Protocol No | FARES         |

S9. Treatment response, defined as effective if no additional hemostatic intervention (such as administration of hemostatic agents including a second dose of IMP, platelet transfusion, or surgical re-exploration) in the time windows

- from 60 minutes to 4 and 24 hours after initiation of the first dose of IMP,
- *from initiation of the first dose of IMP to 4 and 24 hours.*

Otherwise, treatment response will be considered as not effective. If the dose of IMP is repeated within less than 60 minutes, treatment response to the IMP will be assessed as not effective.

Furthermore, the above mentioned efficacy endpoints will be exploratory analyzed in time frames which start at the time of first IMP dosing instead of the start of the surgery (as specified in section 2.2 of this SAP).

The following analysis methods will be applied to the different endpoints in according to their data type:

The analysis of categorical variables (P1, P3, S2, S4, S5, S6) will present relative frequency tables and estimates of the proportions with 95% confidence intervals separately in the treatment groups. The proportions will be compared between the treatment groups by means of Fisher's exact test.

The analysis of continuous variables (S7, S8) will present descriptive statistics of the sampling distribution and the differences between treatment groups. Also 95% confidence intervals and results of t-test of the treatment group differences will be reported.

The analysis of integer count variables (P2, S1, S3) will present descriptive statistics of the sampling distribution and the differences between treatment groups. Treatment group comparisons for variables (P2, S3) will be performed in the context of a counting regression model for the ABPs and their components (SAS PROC GENMOD with Negative-Binomial distribution). Tests and 95% confidence intervals for the treatment group differences will be derived from this statistical model and reported. The analysis for the sum of the allogenic blood products transfused (P2, S3) will be repeated analogously for the adjusted sum of the allogenic blood products transfused (cf. section 6.1), excluding FP.

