##### 3.1.1 Efficacy Endpoints

###### *Primary Endpoints:*

1. Treatment response, defined as effective if no additional hemostatic intervention (such as administration of hemostatic agents including a second dose of IMP, platelet transfusion, or surgical re-exploration) from 60 minutes to 4 and 24 hours after initiation of the first dose of IMP (otherwise will be defined as not effective). If the dose of IMP is repeated within less than 60 minutes, treatment response to the IMP will be assessed for the 60 minutes after the second IMP dose only.
2. Amount of allogeneic blood products (for each type of product and cumulatively) administered during the first 24 hours after the start of surgery.
3. Number of patients who do not receive any RBC transfusions or any allogeneic blood transfusions during the first 24 hours after the start of surgery.

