**5.1.2 Frozen Plasma**

Patients randomized to FP will receive 3 U for IBW≤60 kg or 4 U for IBW>60 kg (corresponding to weight-base dosing range of 10–15 mL/kgIBW rounded up to 1 U increment, up to a maximum of 4 U per dose) for each order during the first 24 hours after randomization. FP will be provided by the Canadian Blood Services and will be stored, thawed, and pooled by the blood bank according to current standards. FP will be infused as per standard hospital protocols at the participating institutions (i.e., infused using timing recommended in the current monograph through standard 140 µm blood infusing set).

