### 6.1.2 Visit 1: First post-randomization visit (0 to 24 hours after randomization)

For any specified activity that cannot be completed on this visit, additional visits will be made until all study data are obtained.

- Obtain consent from patient or surrogate
- Collect baseline data
  - Demographics
  - Medical history
  - Preoperative concomitant medications
- Collect surgical data
  - Intraoperative concomitant medications
  - CPB start and end times
  - Cross-clamp time
  - Circulatory arrest start and end times
  - Fluid in- and output monitoring
  - Inotropes and vasopressors
- Collect laboratory assessments where available as part of routine care
  - Chemistry (sodium, potassium, chloride, bicarbonate, pH)

- Hematology (complete blood count)
  - Coagulation profile before and after IMP administration
  - Safety labs (creatinine, liver function tests [ALT, ALP], bilirubin, troponin)
- Collect all transfusion and hemostatic agents (number and timing) for the 24 hour period after randomization
- Collect bleeding components using the e-CABG and UDPB criteria (1, 72) as well as a modified version of the UDPB not including PCC and FP requirements
- Collect extubation time
- Collect concomitant medications
- Collect AEs and SAEs

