### 3.4 Intention-To-Treat (ITT) Population

The Intention-To-Treat (ITT) population will include all enrolled patients who have given informed consent and who received at least one treatment with either PCC or FP and underwent cardiac surgery. In the event that a patient receives treatment that is not in concordance with the randomization schedule, the treatment group will be defined according to the randomization (rather than the actual treatment received).

|                           |                 |             |               |
|---------------------------|-----------------|-------------|---------------|
| Statistical Analysis Plan | Version 2.0     |             | Page 10 of 19 |
| Sponsor                   | [name] | Protocol No | FARES         |

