| ABP(time frame)                        | = Sum of all Allogenic Blood Products (RBCs, FPs and Platelets) transfused in specified time frame                                                                                                                                                                                                                                                                                                                                                                                                 |
| ABP adj (time frame)        | = Adjusted Sum of Allogenic Blood Products (RBCs and Platelets) transfused in specified time frame, I.e. ABP excluding FPs                                                                                                                                                                                                                                                                                                                                                                         |

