### 6.2 Transformations to be applied

In order that the sum of Allogenic Blood Products and its constituents adequately represent the exposure to donors the following transformations will be applied before any derivations:

Platelets:

1 apheresis unit = 4 allogeneic units,  
1 non-apheresis unit = 4 allogeneic units

Frozen Plasma (used in transfusions):

1 apheresis unit = 2 allogeneic units,  
1 non-apheresis unit = 1 allogeneic unit

Transfusion units without any information about apheresis are handled as apheresis units.

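### The P3 and S4 totals count the control arm's own assigned plasma, so the FP arm scores 0% by construction, and the SAP's plasma-excluded sum does not reach them

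*Combined protocol and SAP*

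**What the plan says.** Protocol section 3.1.1 names as its third primary endpoint "Number of patients who do not receive any RBC transfusions or any allogeneic blood transfusions during the first 24 hours after the start of surgery". SAP section 4.6 carries this forward as "P3. Number of patients who do not receive any allogeneic blood product (in total and for each type separately", with S4 as the same count to postoperative day 7. Both are tested with Fisher's exact test.

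- **What counts.** Protocol section 7.2.2 lists RBCs, platelets and plasma as allogeneic products; PCC is not among them. SAP section 6.1 defines the total as "Sum of all Allogenic Blood Products (RBCs, FPs and Platelets) transfused in specified time frame", with no exception for plasma given as study product.
- **What the control arm receives.** Protocol section 5.1.2: "Patients randomized to FP will receive 3 U for IBW≤60 kg or 4 U for IBW>60 kg".
- **Who is analysed.** The ITT population (SAP section 3.4) is restricted to consenting patients "who received at least one treatment with either PCC or FP and underwent cardiac surgery".
- **The correction in place.** For P2 and S3 only, the analysis is "repeated analogously for the adjusted sum of the allogenic blood products transfused", which is RBC plus platelets with all FP removed (SAP section 6.1).
- **Weighting.** For FP, SAP section 6.2 sets "1 apheresis unit = 2 allogeneic units", and units of unknown type are treated as apheresis.
- **Windows.** The protocol window for P2 and P3 opens at the start of surgery. SAP sections 2.2 and 4.6 add exploratory windows from the end of bypass, from randomisation and from the first dose.

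**The concern.** The control treatment is itself a counted event. A patient assigned to FP and treated as assigned has failed the P3 total as soon as the first dose runs, whatever happens to the bleeding. A PCC patient fails only by needing something more. The comparison can therefore move only towards PCC.

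The protocol sees this problem elsewhere: section 7.2.3 adds a modified UDPB score that omits PCC and FP because randomisation dictates their use. The SAP applies the same logic to the P2 and S3 sums, but not to P3 and S4.

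The pilot exists to select the Phase 3 primary endpoint (protocol section 3.1) and to supply its sample-size inputs (section 1.2). An endpoint that separates the arms with no difference in hemostasis could be chosen for that reason, and Phase 3 would be sized on an artefact.

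**Working it through.** **Inputs.** The plan has no power calculation to reproduce; protocol section 9.1 says the size was not statistically estimated. The only size input is 50 evaluable per arm. (120 randomised to 100 evaluable implies 1 − 100/120 = 16.7% loss, consistent with the stated <20%.) A two-sided 0.05 level is my assumption: the plan states no alpha but uses two-sided 95% intervals.

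**1. P3 total: smallest significant result.** The FP arm is 0/50. With equal arms, the two-sided Fisher p for x/50 against 0/50 is 2 × C(50,x)/C(100,x).
- x = 5: 2 × 2,118,760/75,287,520 = 0.056
- x = 6: 2 × 15,890,700/1,192,052,400 = 0.027

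So 6/50 = 12% in the PCC arm is enough.

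**2. P3 total with no true effect.** Let q be the chance of needing no RBC, platelets or further FP, equal in both arms. The FP arm still scores 0, so the chance of p < 0.05 is P(X ≥ 6), X ~ Bin(50, q).

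| q (assumed) | P(p < 0.05 for PCC) |
|---|---|
| 5% | 3.8% |
| 7% | 13.5% |
| 10% | 38% |
| 15% | 78% |
| 20% | 95% |
| 25% | 99% |

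For scale, protocol section 1.1 cites two propensity-matched studies. RBC transfusion was 84% v 93% in one (225 pairs), so avoidance was 16% v 7%. It was 67.3% v 83.2% in the other (101 pairs), so avoidance was 32.7% v 16.8%. If those rates carry over, they are upper bounds for q, because platelets and further FP must be avoided too.

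**3. After removing assigned plasma.** With the same q in both arms and the FP dose not counted, exact Fisher rejection is 1.3% (q = 7%), 1.8% (10%), 2.5% (16%) and 3.0% (32.7%). The artefact is gone.

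**4. P2 unadjusted total.** One FP dose adds 3–4 units, or 6–8 with the twofold weight. Assuming 40% of patients get 3 U and 60% get 4 U, the mean offset is 0.4 × 3 + 0.6 × 4 = 3.6 (or 7.2). With mean other use m equal in both arms, the FP:PCC ratio is (m + 3.6)/m or (m + 7.2)/m. The cited 225-pair study reports 3.4 and 5.2 RBC units. I also used 8 and 12, since SAP section 6.2 counts each platelet unit as four. Rejection is from a negative-binomial Wald test, 1,000 simulated trials per cell, dispersion 0.5–1.5 (assumed).

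| m | Ratio, ×1 / ×2 | Rejection, ×1 | Rejection, ×2 | Rejection, FP removed |
|---|---|---|---|---|
| 3.4 | 2.06 / 3.12 | 96–100% | 100% | 5–6% |
| 5.2 | 1.69 / 2.38 | 80–98% | about 100% | 6–7% |
| 8 | 1.45 / 1.90 | 50–81% | 93–100% | 5–6% |
| 12 | 1.30 / 1.60 | 29–54% | 70–97% | 5–6% |

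The planned adjusted sum deals with this offset. But it removes all FP, and from the third dose onward both arms receive FP (protocol section 3.2). That plasma reflects continued need and is a real outcome.

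**5. Products given before randomisation.** These are balanced in expectation. If a fraction e of both arms is already exposed, independently of later need, success falls to q(1 − e). At q = 25% the rejection rate in step 2 goes from 99% (e = 0) to 95%, 78% and 38% at e = 20%, 40% and 60%. The effect is dilution.

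For an RBC-avoidance endpoint, required N is proportional to [p1(1 − p1) + p2(1 − p2)]/(p1 − p2)², with both rates multiplied by (1 − e).
- 32.7% v 16.8%: N grows 1.34-fold at e = 20% and 1.92-fold at e = 40%.
- 16% v 7%: N grows 1.29-fold and 1.77-fold.

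**The case against.** The best defence is that SAP section 6.2 says the sums are meant to represent exposure to donors. On that reading, replacing plasma with PCC is the contrast of interest and counting assigned FP is deliberate. This stands as a reason to keep reporting the all-product totals. It does not justify testing them as efficacy, which is where the protocol and SAP place P3.

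Second, the analysis is primarily descriptive, with no alpha, hierarchy or formal claim. That is true and limits the harm. But a between-group p-value on a listed primary endpoint is still what readers will use when choosing the Phase 3 endpoint.

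Third, much is already covered. P2 and S3 have a plasma-excluded repeat. P3 and S4 are also reported by product type, and the RBC and platelet rows carry no artefact. Windows from randomisation and from the first dose are planned. All of this stands. What remains open is the P3/S4 total and the FP-only row. The windows from randomisation and from the first dose do not help there, because both contain the assigned plasma.

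Finally, SAP section 6.2 labels its plasma line as plasma used in transfusions, which might be read as leaving study plasma out. The definition in section 6.1 counts every product without exception, so the plan needs to say which is meant.

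**Conclusion.** The point holds for the P3 and S4 totals and their FP-only rows: the FP arm's value and the direction of the comparison are fixed by design. The unadjusted P2/S3 total carries the same offset, at least 3–4 units per assigned dose, and already has a correction that removes slightly too much. This should be fixed, but it does not undermine the trial. It rests on patients being treated as assigned and on the section 6.1 definition applying to study plasma; the rejection rates also rest on the assumed q and on 50 per arm.

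Four stronger readings are tempting and not supported.
- **That significance is decided by design.** It is not: at q of 10% or less the test usually does not reject.
- **That the start-of-surgery window also favours PCC.** Products given before randomisation only dilute the contrast.
- **That the unadjusted P2 test would almost always reject.** Under the assumptions shown, rejection with single weighting runs from 29% to 100%.
- **That the window would double or triple Phase 3.** Squaring the shrinkage alone gives 1/(0.8)² = 1.56 to 1/(0.6)² = 2.78, but the variance shrinks too. About 1.3 to 1.9-fold follows from the cited rates, and only if 20–40% are exposed beforehand, a figure the documents do not give.

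**What to change.** In SAP sections 4.6 and 6.1, define a non-IMP total: RBC, platelets and any FP given outside the two assigned doses, derived identically in both arms.

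- Use it for the between-group tests of the P3 and S4 totals.
- Use it in place of the present adjusted sum for P2 and S3.
- Report the all-product totals, and the FP-only row of P3/S4, descriptively as donor exposure and not as hemostatic efficacy.
- State in section 6.2 whether the plasma weighting applies to study plasma.
- Record the change of tested total in section 2.2, which now reports no deviation from the protocol's methods.

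The protocol's start-of-surgery window can stay. When choosing and sizing the Phase 3 endpoint, read the already planned results for 24 hours after randomisation alongside it.

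The cost is SAP wording and one derived variable. Visit 1 already requires sites to "Collect all transfusion and hemostatic agents (number and timing) for the 24 hour period after randomization", and SAP section 4.3 summarises study doses, so FP units should be attributable to an assigned dose or not. The downside is that the tested total is no longer directly comparable with literature that counts all plasma; the descriptive totals keep that link.
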